### Study objectives

The overall aim of this study is to recommend the best diagnostic methods to monitor drug efficacy and status of AR in STH programs. These will then be applied in work package 2 (the establishment of a surveillance system to monitor the global patterns of drug efficacy and emergence of AR in STH programs). The specific objectives are to:
Assess equivalence of ERRs measured by Kato-Katz thick smear, Mini-FLOTAC and FECPAK^G2^Assess the diagnostic performance of Kato-Katz thick smear, Mini-FLOTAC, FECPAK^G2^ and qPCRAssess the costs linked with assessing drug efficacy by Kato-Katz thick smear, Mini-FLOTAC and FECPAK^G2^Provide proof-of-principle for qPCR to assess intensity of infection and drug efficacyAssess associations between frequency of SNPs linked to BZ resistance measured by pyrosequencing and history of drug pressure and drug efficacyCompare pyrosequencing and LAMP for the assessment of SNPs linked to BZ resistanceAssess pooling samples as a cost-saving strategy to determine infection intensity (qPCR) and frequency of SNPs linked to BZ resistance (pyrosequencing and LAMP)

## Methods

### Ethics approval and consent to participate

The Starworms protocol has been reviewed and approved by the Institutional Review Board (IRB) of the faculty of medicine of Ghent University, Belgium (Ref. No B670201627755). The trial protocol was subsequently also reviewed and approved by the IRBs associated with each trial site (Ethical Review Board of Jimma University, Jimma, Ethiopia: RPGC/547/2016; National Ethics Committee for Health Research (NECHR), Vientiane, Lao PDR: 018/NECHR; Zanzibar Health Research Council, United Republic of Tanzania: ZAMREC/0002/February/2015 and the Institutional Review Board from Centro de Pesquisas René Rachou, Belo Horizonte, Brazil: 2.037.205).

Parent(s)/guardians of participants will sign an informed consent document indicating that they understand the purpose of and procedures required for the study and that they are willing to have their child participate in the study. If the child is ≥5 years, he/she has to orally assent in order to participate in the study. Participants of ≥12 years of age are only included if they sign an informed consent document indicating that they understand the purpose of the study and procedures required for the study and are willing to participate in the study.

### General design of the field trials

A series of drug efficacy trials will be performed in four STH endemic countries (Brazil, Ethiopia, Lao PDR and Tanzania). These trials will be designed to assess the efficacy of a single oral dose of 400 mg ALB against STH infections in SAC by a variety of stool-based diagnostic methods. At the start of each trial, schools will be visited by the local principal investigator (PI) and a team of field officers, who will explain the planned trial and sampling method to the parents and teachers and the children. At baseline, SAC will be asked to provide a fresh stool sample. All children that meet all inclusion criteria and none of the exclusion criteria (see Table 1) will be enrolled in the study. They will be treated with a single oral dose of 400 mg ALB under supervision. The ALB to be used in the different studies is manufactured by GlaxoSmithKline and donated to WHO and originates from the same production batch (Batch Nr: 335726). All collected stool samples will be processed to determine the fecal egg counts (FECs; expressed in eggs per gram of stool (EPG)) for each STH using Kato-Katz thick smear (single and duplicate), Mini-FLOTAC and FECPAK^G2^. During baseline evaluation, only stool samples found to contain at least 13 eggs on duplicate Kato-Katz or at least 15 eggs on Mini-FLOTAC for at least one of the three STHs will be preserved for further molecular analysis. Fourteen to 21 days after drug administration, a second stool sample will be collected from all the children that were excreting eggs of any STH at baseline based on Kato-Katz thick smear and Mini-FLOTAC. Stool samples will be examined by Kato-Katz thick smear (single and duplicate), Mini-FLOTAC and FECPAK^G2^. All follow-up samples will be preserved for further molecular analysis. To gain insights into the operational costs for assessing drug efficacy, the time to process stool with Kato-Katz thick smear, Mini-FLOTAC and FECPAK^G2^, and the time needed to enter data and to draft reports will be assessed. The different steps of the trials are schematized in Fig 1.

**Fig 1 pntd.0006912.g001:**
[figure not shown]
A schematic overview of the different steps of the field trials.

**Table 1 pntd.0006912.t001:** Inclusion and exclusion criteria to be followed during the recruitment of participants for the field trials.

Inclusion criteria	Exclusion criteria
Subject is 5–14 years of age Subject is otherwise in healthy condition (based on medical history and physical examination) Parent(s)/guardian(s) of subject signed an informed consent document indicating that they understand the purpose of and procedures required for the study and that they are willing to have their child participate in the study Subject of ≥5 years has assented to participate in the study Subject of ≥12 years has signed an informed consent document indicating that they understand the purpose of the study and procedures required for the study, and are willing to participate in the study Subject has provided a stool sample of at least 9 grams.	Subject has active diarrhoea (defined as the passage of 3 or more loose or liquid stools per day) at baseline or follow-up. Subject has an acute medical condition or is experiencing a severe concurrent medical condition Subject has a known hypersensitivity to ALB or MEB Subject has received anthelmintic treatment within 90 days prior to the start of the treatment Subject vomited within 4 hours following drug ingestion. Subject is not able to provide a stool sample of min 9 grams at baseline or follow-up. Subject has not swallowed the entire tablet.

### Study population

The study will focus on SAC (age 5–14) since they are the major target of PC programs targeting STH, and they usually represent the group with highest worm burdens for *A*. *lumbricoides* and *T*. *trichiura* [56]. This study will be conducted in Ethiopia, Tanzania, Lao PDR and Brazil. The selection of these sites is based on their experience in assessing drug efficacy [13, 15], evaluating the performance of diagnostic methods [57–59] and the availability of well-equipped diagnostic facilities and skilled personnel, and PC history (Table 2).

**Table 2 pntd.0006912.t002:** An overview of the countries, study sites and institutions involved in work package 1 of the Starworms project as well as their respective drug pressure and the type of benzimidazole drug administered.

Country	Study site	Institution	Drug Pressure *	Drug
**Brazil**	Americaniñas, Belo Horizonte	Fiocruz—Research institute of Renê Rachou	Low	ALB
**Ethiopia**	Jimma Town, Jimma Zone	Jimma University	Low	ALB
**Lao PDR**	Nam Bak, Luang Prabang	National institute of public health	Medium	MEB
**Tanzania**	Chake Chake, Pemba	Public Health Laboratory—Ivo de Carneri	High	ALB

* The classification of the countries into the four levels of drug pressure was based on the reported national coverage of drug administration to preschool (preSAC) and school aged children (SAC) for the last 5 years (2009–2014; Preventive Chemotherapy Database of the WHO). Very high drug pressure: coverage >80% for preSAC and SAC for each of the last 5 years; moderately high: coverage >50% for preSAC and/or SAC for each of the last 5 years; moderate: coverage >30% for preSAC or SAC for each of the last 5 years; low: coverage is <30% for both preSAC and SAC for each of the last 5 years.

### Sample size calculation

A sample size was calculated to test the alternative hypothesis that FECPAK^G2^, Mini-FLOTAC and single Kato-Katz thick smear provide equivalent drug efficacy results measured by ERRs compared to a duplicate Kato-Katz thick smear. Given the differences in drug efficacy of ALB across the STH species [15, 21] (*Ascaris*: ~99%, hookworms: ~96%, *Trichuris*: ~65%), a level of equivalence that is acceptable for *Trichuris* may not be acceptable for *Ascaris*. Therefore, a species-specific level of equivalence was used. For *Ascaris* the level of equivalence was set at 2.5-point percentage, for hookworms and *Trichuris* the level of equivalence was set at 5.0 and 10 point percentage, respectively. Both type I and II errors were set at 0.05.

To calculate the corresponding sample size for each of the STH species, we performed a simulation study. This simulation study considered (i) variation in ERR and baseline FECs across and within STH species, (ii) variation in FECs introduced by the egg counting process, (iii) the paired ERR results across egg count methods, and (iv) a post-hoc correction for a pair-wise comparison. Based on the simulation, at least 110, 100 and 12 complete cases are required for *Trichuris*, hookworm and *Ascaris*, respectively. A detailed description of the sample size calculation is available in the supplementary information (S1 Info).

### Laboratory procedures

We will provide participants with a container for the collection of stool samples. The samples will be collected and stored in cooler boxes with ice-packs, which will then be transported to the laboratory at the respective study site for further analysis. Upon arrival in the laboratory, samples will be thoroughly homogenized using a wooden spatula to obtain a more homogeneous distribution of STH eggs in the stool [60]. A detailed standard operating procedure (SOP) on sample homogenisation is available in the supplementary information (S2 Info).

### Egg counting methods

#### Kato-Katz thick smear

Kato-Katz thick smears will be prepared on microscope slides using a square template with a hole of 6 mm diameter and 1.5 mm deep, which is assumed to sample 41.7 mg of stool [61]. Two Kato-Katz thick smears will be prepared per sample (slide A and B) and to avoid clearing of hookworm eggs, all slides will be examined within 30–60 min for the presence of STH eggs. The number *A*. *lumbricoides*, *T*. *trichiura* and hookworm eggs will be counted and recorded per slide. Slide A will represent a single Kato-Katz thick smear. For the duplicate Kato-Katz thick smear, the egg counts of slide A and B are added and multiplied by 12 to obtain the FEC. A detailed SOP on how the duplicate Kato-Katz thick smears will be processed is provided in S3 Info.

#### Mini-FLOTAC method

The Mini-FLOTAC method will be performed as described earlier [62]. In short, the sample recipient of the Fill-FLOTAC will be filled with fresh stool. Subsequently, the stool will be thoroughly homogenized with 38 ml of flotation solution (FS) (saturated salt solution, density = 1.20). The suspension will then be filtered through the integrated Fill-FLOTAC filter, and transferred into the two chambers of the Mini-FLOTAC device. After 10 minutes, the top part of the chambers will be translated, and both chambers of the Mini-FLOTAC device will be screened for the presence of STH eggs under a light microscope using a 100x magnification. The number of eggs in both Mini-FLOTAC chambers combined will be counted and recorded for *A*. *lumbricoides*, *T*. *trichiura* and hookworm, separately. A detailed SOP on the Mini-FLOTAC method can be found in the supplementary information (S4 Info).

#### FECPAK^G2^ method and automated egg counting

Ayana et al. (in press) [36] describes the FECPAK^G2^ method for counting STH eggs in human stool. Stool analysis starts by weighing 3 grams of fresh stool in a Fill-FLOTAC. Subsequently, the stool will be homogenized in tap water. Afterwards, the stool suspension will be transferred to the FECPAK^G2^ sedimenter and additional tap water will be added to the sedimenter (approximately 200 ml). The sedimenter will be inverted 3 times to mix the solution, after which it will be placed on an even surface at room temperature to allow STH eggs to sediment. The next day, the supernatant will be poured off and 80 ml FS will be added to the remaining slurry (15 ml) that is being retained in the bottom of the sedimenter by the plastic dam. The whole content of the sedimenter will then be poured into a FECPAK^G2^ filtration unit. The closed FECPAK^G2^ filtration unit will be inverted three times before transferring 455 μl of the suspension into each of the 2 wells of the cassette. Between each sampling, the cylinders will be inverted three times to homogenize the solution. After filling the wells, the cassette will be placed on a horizontal surface for a minimum of 20 minutes to allow accumulation of the STH eggs around the tip of the rod that is present in the centre of each well of the FECPAK^G2^ cassette. Subsequently, the cassette will be placed in a Micro-I device for image capture, which will be connected to a laptop or desktop computer. The device automatically images both wells. The digital images of the wells will be stored on the laptop / computer and will be uploaded to the main FECPAK^G2^ server when an Internet connection is available. After the imaging step, the cassettes will be emptied and rinsed with tap water for reuse. To count the eggs, sample images and details (sample ID, sample collection date, study site, etc.) will be uploaded from the server. Finally, the mark-up technician will identify and count any STH eggs present in the images using specialized software developed for this purpose. Results of the mark-up will be saved and stored automatically for reporting and analysis. Detailed SOPs on how to perform the FECPAK^G2^ and to mark-up the images are available in S5 Info. Stored images will also be submitted for analysis by specialized image processing software originally designed to detect and quantify helminth eggs in waste water [35].

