A method that largely meets this target product profile is the FECPAK^G2^ platform. Recently, it has been launched as a complete remote-location diagnostic method for sheep/cattle farmers and their veterinarians to assess the intensity of helminth infections and efficacy of drugs [33]. The platform accumulates helminth eggs into one microscopic view after which digital images are taken [34]. Images are stored by the associated software and can be uploaded to a remote server when an Internet connection is available. Later, a web-based laboratory technician can count the eggs visible in the images, after which the results are returned to the user by e-mail. The FECPAK^G2^ platform thus potentially eliminates the need for skilled technicians on-site. The online software allows easy access for quality control of egg counting and the production of standardized analysis and reports. More importantly, it opens the door to automated egg counting by egg recognition software [35]. Recently, Ayana et al. (in press) [36] modified and optimized a FECPAK^G2^ protocol for the detection and quantification of human STH eggs in stool. However, it remains unclear whether it provides equivalent ERR results to those obtained by diagnostic methods recommended by WHO, and whether it would result in more efficient use of financial and technical resources under field conditions.

From a research perspective, there is a growing interest to apply quantitative polymerase chain reaction (qPCR) for the assessment of drug efficacy. In contrast to the egg counting methods, qPCR can differentiate the different hookworm species, and thus allow evaluation of BZ efficacy against the different hookworm species [37, 38]. This is of particular interest given that there could be differential susceptibility towards BZ drugs among hookworm species, and that there is increasing evidence of zoonotic transmission of *Ancylostoma ceylanicum* between dogs and humans [39–42]. Although studies have linked amount of DNA with egg output [37, 43], to date, qPCR has not yet been applied for the assessment of drug efficacy.

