#### Quality control egg counting procedure

A predefined, randomly selected subset of samples (10% of the total number of samples) will be re-evaluated by each of the three egg count methods. To this end, a senior researcher, who is blinded to the initial FECs, will re-count STH eggs across all three egg count methods. A third examiner will re-count STH eggs in case of discrepancies. Discrepancies are defined as (i) false negatives/positives, (ii) difference in egg counts >10 when the total number of eggs counted ≤100 or (iii) difference in egg counts >20% when more than 100 eggs are counted [24]. A detailed SOP on the performance of quality control for the egg counting methods is provided in the supplementary information (S6 Info).

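### FECPAK^G2^ images are loaded for counting with collection date and study site, and the article states neither masking to visit nor a mixed reading order; the risk matters mainly for Trichuris

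*Protocol article*

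**What the plan says.** The section on the FECPAK^G2^ method describes the counting step in two sentences. First, "sample images and details (sample ID, sample collection date, study site, etc.) will be uploaded from the server". Then "the mark-up technician will identify and count any STH eggs present in the images using specialized software developed for this purpose". The details that travel with the images therefore include the collection date and the site, with an open-ended remainder. Detailed SOPs on how "to mark-up the images are available in S5 Info", which is not shown.

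Under General design of the field trials, the timing is fixed: "Fourteen to 21 days after drug administration, a second stool sample will be collected from all the children" who were egg-positive at baseline. Every follow-up image thus comes from a treated child.

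The one blinding statement for egg counting is in the quality control section, where "a senior researcher, who is blinded to the initial FECs, will re-count STH eggs across all three egg count methods". It covers 10% of samples and concerns the first count, not the visit. The article states no masking to visit and no reading order for any egg counting method.

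**The concern.** The ERR compares the mean egg count at follow-up with the mean at baseline. Two separate mechanisms could make detection differ between visits:

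- **Expectation.** A technician who knows that an image was taken after treatment knows which way the count should have moved. Visible dates, sites or sample IDs could feed this.
- **Reading order.** If all baseline images are read before the follow-up images, any change in the technician's performance over time coincides with the visit. This does not depend on a visible date, and hiding the date would not remove it. The Introduction says the protocol for human stool was only recently modified, which makes a change in performance conceivable but does not show one.

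At stake is the first specific objective, equivalence of FECPAK^G2^ with duplicate Kato-Katz in ERR, for which the sample size was calculated. FECPAK^G2^ is also the method where protection is easiest, since its images are stored and read afterwards: "Later, a web-based laboratory technician can count the eggs visible in the images".

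**Working it through.** **Inputs from the article.** Planning ERRs are about 65% (Trichuris), 96% (hookworm) and 99% (Ascaris). Equivalence margins are 10, 5 and 2.5 percentage points (both from Sample size calculation). The ERR formula uses arithmetic means (equivalence analysis section). The article gives no reader-error rate, so there is no stated figure to reproduce, and the undercounts below are assumptions. The sample sizes rest on S1 Info, which is not shown, and are not in question here.

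**Formulas.** Let *r* be detection at follow-up divided by detection at baseline.

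- Measured ERR = 1 − (1 − ERR) × *r*. If *r* = 1, the detection rate cancels.
- Undercount *b* at follow-up only: *r* = 1 − *b*.
- Undercount *c* at baseline only: *r* = 1/(1 − *c*).

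**Trichuris at selected values of *r*.**

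- *r* = 0.85: 1 − 0.35 × 0.85 = 70.25% (+5.25 points).
- *r* = 0.70: 1 − 0.35 × 0.70 = 75.5% (+10.5, beyond the margin).
- *r* = 1.25: 1 − 0.35 × 1.25 = 56.25% (−8.75).

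**Shift in ERR (points) for undercounts of 5 / 10 / 20 / 30% at one visit.**

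| Species (margin) | At follow-up only | At baseline only |
|---|---|---|
| Trichuris (10) | +1.75 / +3.5 / +7.0 / +10.5 | −1.84 / −3.89 / −8.75 / −15.0 |
| Hookworm (5) | +0.2 / +0.4 / +0.8 / +1.2 | −0.21 / −0.44 / −1.0 / −1.71 |
| Ascaris (2.5) | +0.05 / +0.1 / +0.2 / +0.3 | −0.05 / −0.11 / −0.25 / −0.43 |

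**Undercount that uses up the whole margin.**

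- Trichuris, follow-up: 0.10/0.35 = 28.6%. Trichuris, baseline: 1 − 0.35/0.45 = 22.2%.
- Hookworm, baseline: 1 − 0.04/0.09 = 55.6%. Ascaris, baseline: 1 − 0.01/0.035 = 71.4%.
- Follow-up undercounting alone can raise the ERR by at most 4 points (hookworm) or 1 point (Ascaris), both inside the margin.

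**Effect on the difference from Kato-Katz.** If Kato-Katz has its own ratio *r*~K~ and FECPAK^G2^ has *r*~F~, the spurious difference (FECPAK^G2^ minus Kato-Katz) is (1 − ERR) × (*r*~K~ − *r*~F~). For Trichuris with *r*~F~ = 0.70 and *r*~K~ = 0.85, this is 0.35 × 0.15 = 5.25 points. Equal ratios cancel fully.

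**Effect on the efficacy class (Table 4).** At a Trichuris ERR of 65%, the class leaves satisfactory only if *r* exceeds 0.50/0.35 = 1.43, that is, a baseline undercount above 30%. A smaller change suffices only where the true ERR lies nearer a threshold.

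**Would the recount catch it?** Up to 100 eggs, a recount is discrepant if positivity differs or the counts differ by more than 10 eggs. From the FECPAK^G2^ section, 2 × 0.455 ml is read from 15 + 80 = 95 ml holding 3 g of stool: 3 × 0.91/95 = 0.0287 g, so one egg stands for about 35 EPG. A Trichuris infection at the top of the light class (999 EPG) gives about 999/34.8 = 28.7 eggs at full recovery, and fewer otherwise. A 28.6% undercount of these is about 8 eggs, below the trigger. In heavier infections the trigger would be reached: 10/0.286 = 35 eggs, or about 1,220 EPG.

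**The case against.** The strongest reply is that the article leaves the mark-up procedure to S5 Info, where coding, masking and reading order belong. That stands as a limit. A reader might infer that the technician is shown the visit and that the FECPAK^G2^ ERR is therefore biased. The article supports neither: it says the details are loaded for counting, not that they are on screen, and it reports no reader error. What remains is that the workflow, as described, puts identifying details at the counting step, and the only blinding mentioned addresses something else.

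Date and site need not reveal the visit either. Each trial covers several schools, and with staggered starts one school's baseline may overlap another's follow-up. This stands in part, but the sample ID and unspecified further details travel with the image too.

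A reader might also take the weakness to be peculiar to FECPAK^G2^. It is not. Kato-Katz slides are examined within 30–60 minutes, so those readers necessarily work in visit order, and no masking is stated for them. Shared expectation would partly cancel in the difference. Masking FECPAK^G2^ alone could even expose a Kato-Katz bias that was cancelling before. This is fair, but cancellation needs similar ratios in different readers using different techniques, and nothing in the plan secures that. FECPAK^G2^'s own ERR, and its class when close to a threshold, would be affected regardless.

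Finally, a Trichuris reader who expects about a third of eggs to remain has little reason to expect empty images, so expectation may be weak in the one species where it could matter. That is reasonable; the reading-order mechanism does not depend on it. The 10% recount is a partial safeguard for heavier infections. The additional analysis of the images by software is not named as the source of the FECPAK^G2^ ERR.

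**Conclusion.** The point holds as a risk in the stated workflow, not as a demonstrated bias. As described, the mark-up technician may be able to tell baseline from follow-up images, and nothing stated keeps reading order separate from visit.

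The possible effect is material mainly for Trichuris: one-sided undercounts of roughly 22–29% would consume the 10-point margin, and 10% would consume 3.5 to 3.9 points of it. These error rates are assumptions, and the full shift reaches the comparison only if duplicate Kato-Katz has no matching shift. A wider reading, that equivalence is in doubt for all three species, is not supported: for hookworm and Ascaris, undercounts of up to 30% stay well inside the margins. If S5 Info already masks and mixes the images, the point reduces to a missing cross-reference.

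**What to change.** If S5 Info already provides masking to visit and a mixed reading order, say so in the FECPAK^G2^ section. Otherwise:

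- Give each image set a random code, with the key held by the coordinating team.
- Hide collection date, visit and site from the mark-up technician.
- Mark up the baseline and follow-up images of a site together in random order. This deals with reading order, which hiding the date does not.
- Have both visits of a child read by the same technician, so that differences between technicians do not fall on one visit.
- State whether the quality control re-reader is masked to visit for the image-based counts.
- Acknowledge in reporting that Kato-Katz cannot be shuffled across visits, so a bias in the comparator may remain in the difference.

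No extra samples or stool examinations are needed. The costs are a coding step, which must be feasible on the FECPAK^G2^ server (the article does not say whether it is), an SOP change, and FECPAK^G2^ counts that become available only after follow-up sampling at a site. That delay does not hold up the trial, because the children followed up are those "excreting eggs of any STH at baseline based on Kato-Katz thick smear and Mini-FLOTAC", not those positive on FECPAK^G2^.
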